### Group A: Flow-controlled ventilation

For the safety of the staff, only the investigators will be in the room and perform the change to the Tritube. This will be done under full PPE.

Via the existing tube the ultra-thin Tritube will be inserted. For this purpose, the existing tube will be clamped, and the ventilator will be set on hold. Then the connector with the inlet for the tritube will be connected and the Tritube will be inserted. Hereafter, the clamp will be removed, and the ventilator will be re-started. Then the Tritube will be advanced, blocked and connected to the Evone-ventilator. The ventilator settings will be started with the pre-existing-PEEP and the standard ventilator will be set on hold. The upper pressure will be determined to achieve a tidal volume of 6 ml/kg lean body mass, while the respiratory rate will be set to maintain an arterial BGA?? above 7.2 pH.

### Group B: standard care (pressure-controlled ventilation)

In this group the ventilator settings will be adjusted by the ICU team (respiratory therapist) in agreement with lung-protective ventilation strategy [3a,4].

All other treatment will be unchanged and according to our local policies/guidelines.

In all groups the first clinical data collection starts after 1 hour of initiation of the “new” ventilation strategy.

The study ends at 48 hours after insertion of the Tritube or if the patient deteriorates needing prone-positioning or ECMO therapy.

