### Methods:

After admission to the ICU, the patients will receive information about the study and informed consent will be taken. Upon reaching the criteria for moderate to severe ARDS (P/F ratio below 200 mmHg and PEEP above 5 cmH2O) the patients will be randomized. In the treatment group (group A) the ultra-thin ventilation tube will be placed through the existing tube. Then flow-controlled ventilation will be applied for 48 hours. In the other group (group B) ventilation will be performed according to the lung protective strategy. All other treatment will be unchanged.

Data-collection will be started 1 hour after initiation of the study.

Primary end point is PaO2.

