#### 4. Objectives

##### Primary outcome:

We choose as the primary endpoint arterial oxygen partial pressure ( $\text{PaO}_2$ ).

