##### Secondary Outcomes:

- Minute volume
- Tidal volume
- Respiratory rate
- Intertidal tracheal pressure amplitude
- Peak airway pressure
- End-tidal  $\text{CO}_2$
- Chest wall compliance
- Respiratory resistance
- Inhaled oxygen fraction ( $\text{FiO}_2$ )
- Arterial  $\text{CO}_2$  ( $\text{PaCO}_2$ )
- Tube obstruction by secretion

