## **9. Statistical Consideration and Data Analysis**

Power-calculation: In order to keep the total number of patients small we will match the patients according to age, co-morbidities inhaled oxygen fraction and we regard this investigation as a feasibility study. Therefore, the sample size calculation based on the assumption of an effect size (change in PaO2) of 1.5 SDS in the primary endpoint (PaO2), an intended power of 80%, an alpha error of 5% and an equal sample ratio results in n=7 patients needed to treat. However, to compensate for dropouts we will include 10 patients in each group, which means in total 20 patients.

Data analysis: Categorical data will be presented as number and percentage, while interval data will be presented by median and interquartile range (IQR). Normally distributed data will be analyzed by using two-tailed unpaired Students t-test. Continuous variables with skewed distribution will be analyzed using Mann-Whitney U testing and dichotomous variables by means of Fisher's exact test. A p-value <0.05 is considered significant. All data analyses will be done using SPSS version v26 (IBM Corp, Armonk NY, USA). Graphs will be constructed using GraphPad Prism (GraphPad Prism version 5.0a for Windows, GraphPad Software, San Diego CA, USA).

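### The 48-hour observation window hangs on Tritube insertion, so it is undefined for all of group B and for any group A patient whose Tritube is never placed

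*Protocol*

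**What the plan says.** The primary endpoint is given in section 4: "We choose as the primary endpoint arterial oxygen partial pressure". It carries no time point, so the observation window alone decides which blood gases can count.

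Section 6 sets the order of events. Patients are randomised once they meet the ARDS criteria, and the Tritube is then passed through the existing tube in group A. Under the group B heading, the same section starts data collection in all groups one hour after the new ventilation strategy is begun, and then ends the study: "The study ends at 48 hours after insertion of the Tritube or if the patient deteriorates needing prone-positioning or ECMO therapy".

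The Methods part of the synopsis takes delivery of the device for granted: "Then flow-controlled ventilation will be applied for 48 hours". Section 4 nevertheless lists a device problem among the secondary outcomes: "Tube obstruction by secretion". Section 5 has blood gases and respiratory parameters recorded every 6 to 8 hours as clinical routine.

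Section 9 justifies the sample size ("an intended power of 80%, an alpha error of 5% and an equal sample ratio results in n=7 patients needed to treat") and then adds a reserve: "However, to compensate for dropouts we will include 10 patients in each group, which means in total 20 patients". It does not say what makes a patient a dropout.

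**The concern.** An observation window in a randomised trial should open and close on events that both arms have. Here the 48-hour clock starts on an event that only group A can have, and that not every group A patient need reach. Two gaps follow. Group B has no stated 48-hour end, so the period over which its PaO2 is compared with group A's is left to the person collecting the data. A group A patient with a failed placement has no window at all.

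The second gap is the more serious. It is a post-randomisation loss that cannot occur in group B, in an unblinded trial of 10 patients per arm. If patients in whom placement fails also tend to have poor oxygenation, losing them raises the group A mean without any effect of FCV.

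**Working it through.** **Step 1. Apply the window in section 6 to each kind of patient.**

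| Patient | Start of collection | 48-hour end |
|---|---|---|
| A, Tritube placed, FCV continues | 1 h after FCV starts | 48 h after insertion |
| A, Tritube placed, FCV stopped early | 1 h after FCV starts | 48 h after insertion, still defined |
| A, Tritube never placed | none | none |
| B | 1 h after the new strategy, an event not identified for patients on standard care | none |

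For the last two rows, the only stated ending is prone positioning or ECMO.

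**Step 2. Reproduce the plan's sample size.** Inputs from section 9: effect 1.5 SD, power 80%, alpha 5%, equal allocation, and a two-sided test ("two-tailed unpaired Students t-test"). With the normal approximation,

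n per group = 2(1.960 + 0.842)² / 1.5² = 2 × 7.85 / 2.25 = 6.98, so 7.

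The stated 7 is reproduced. Enrolling 10 leaves a reserve of 3 of 10 per arm, and 7 / (1 − 0.30) = 10. The protocol gives no device-failure rate, so I take 0 to 3 failures in group A, where 3 is the whole reserve of one arm.

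**Step 3. Failures excluded from group A.** Assumptions: 10 per arm before exclusion, normally distributed PaO2, SD set to 1, two-sided unpaired t-test. Bias and false-positive rates come from 200,000 simulated trials with no true effect, removing the k group A patients who score worst on a marker correlated with PaO2. The false-positive rate counts only significant results favouring FCV (nominal 2.5%).

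| Link between failure and low PaO2 | Bias in SD, k = 1 / 2 / 3 | False positives for FCV, k = 1 / 2 / 3 |
|---|---|---|
| None | 0 / 0 / 0 | 2.5% / 2.5% / 2.4% |
| Correlation 0.3 | 0.05 / 0.09 / 0.14 | 3.2% / 3.8% / 4.5% |
| Correlation 0.7 | 0.12 / 0.22 / 0.32 | 4.6% / 6.9% / 9.5% |
| Lowest values always lost | 0.17 / 0.32 / 0.46 | 6.2% / 11.0% / 16.5% |

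As a check, the bias should equal the correlation times the worst case: 0.7 × 0.317 = 0.22 for k = 2, and 0.3 × 0.456 = 0.14 for k = 3. Both agree.

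Power is not the main issue. If failures are unrelated to PaO2, t-test power at 1.5 SD is 86.8%, 84.3% and 81.2% for 9, 8 and 7 patients against 10, compared with 88.7% for 10 against 10.

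**Step 4. Failures kept in group A.** If a failed patient gains nothing from FCV, the expected difference is 1.5 × (1 − k/10), that is 1.35, 1.20 or 1.05 SD. Power is then about 78%, 65% or 51%. These figures are the price of keeping everyone, not harm done by the present text.

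**The case against.** The strongest reply is that the protocol nowhere says device failures are dropouts or are excluded. That is correct. A sample-size allowance is compatible with analysing everyone as randomised, and the analysis population is commonly left to a SAP, which is not shown. A reader might infer from section 9 that device failures are meant to use up the reserve, but the text does not support this. It only leaves the possibility open.

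A reader might also infer that a patient whose tube later obstructs leaves the comparison. The text points the other way: neither obstruction nor stopping FCV is listed as an end of study. Once a Tritube has been inserted, the patient stays in until 48 hours (barring prone positioning or ECMO), with routine blood gases available. The listing of obstruction as a secondary outcome says that it will be recorded, not that it ends FCV.

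Thirdly, the synopsis gives another start for data collection, one hour after the study is initiated, and this could be read as common to both arms. It does not say what initiation means, differs from section 6, and supplies no 48-hour end for group B.

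Finally, the bias depends on assumptions and may be zero. That stands too. What survives is the window itself: it is protocol text about when data are collected, and a SAP would have to work around it.

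**Conclusion.** The point holds for the window. As section 6 is written, the 48-hour end is undefined for every group B patient, and both start and end are undefined for a group A patient who never receives a Tritube. Such a patient contributes no PaO2 if the text is followed, and could be treated as a dropout in one arm only.

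The size cannot be fixed from the protocol. For 1, 2 or 3 exclusions among 10 group A patients, the bias runs from 0 SD when failure is unrelated to PaO2 up to 0.17, 0.32 or 0.46 SD towards FCV when the lowest values are always the ones lost. Against the planned effect of 1.5 SD, the upper end is material but not dominant. The direction rests on failures having low PaO2, and it would reverse if they had high PaO2. It would therefore go too far to say that the plan breaks randomisation in favour of FCV. It leaves room for that to happen.

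**What to change.** In section 6, start the PaO2 window and the 48-hour observation clock at randomisation, or at one event that both arms share. State that the routine 6- to 8-hourly blood gases continue to 48 hours in the allocated arm, whether or not the Tritube was placed or FCV continued. This concerns data collection only and changes no treatment rule. The ending at prone positioning or ECMO can occur in either arm and lies outside this point.

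In section 9, say that failed placement or early cessation of FCV is not a dropout. Record the time and reason of each and report them as feasibility results, which suits a study that describes itself as one of feasibility.

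The cost is a few sentences and one extra analysis, since the blood gases are already taken. The downside is dilution if devices fail. That is conservative for the aim in section 3, which is to show a positive effect on oxygenation, but it can favour the non-inferiority aim in the synopsis. An analysis restricted to readings taken on FCV should therefore be shown beside the main one.

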## 5. Variables

We will collect demographic data (age, sex, BMI), co-morbidities and clinical data (need for special intervention, e.g. “proning”) drugs used and fluids administered.

Next to the vital parameters (blood pressure, heart frequency and body temperature) the oxygenation parameters (BGA) will be collected 6-8 hourly according to clinical standard.

Kidney-function parameters (creatinine, urea), liver function tests and whole blood counts and immune-parameters like interleukin 6 (IL-6) will be recorded.

Cardiac enzymes will be collected (troponin, BNP) will be evaluated and reported on clinical need.

All of these parameters are reported routinely on daily base for clinical purpose.

Demographic parameters:

- Age
- Gender
- Body Mass Index (BMI)
- Co-morbidities
- Drug history

Laboratory parameters (routinely sampled):

- Coagulation parameters (aPTT, INR/PT, fibrinogen levels, D-dimer)
- Whole blood count (including differential blood count)
- Metabolic parameters (Creatinine level, LDH, liver function tests, albumin level)
- Lactate level
- CRP, IL-6
- Troponin

Clinically parameters:

- Timing of clinical course (e.g. admission, ICU admission, intubation, ECMO)
- Time of intubation
- Time to extubation
- SOFA score

The following respiratory parameters will be recorded together with the BGA (6-8 hourly):

- Pressure during inspiration (PIP)
- Positive End-Expiratory Pressure (PEEP)
- Lung compliance
- Minute volume
- Tidal volume
- Respiratory rate (RR)
- Intratracheal pressure amplitude
- Peak airway pressure
- End-tidal CO2
- Chest wall compliance
- Respiratory resistance
- FiO2

- I: E ratio
- ABG

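### Study observation ends when a patient deteriorates to proning or ECMO, so a PaO2 comparison late in the 48 hours can be biased, and enrolling more patients does not correct this

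*Protocol*

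**What the plan says.** Section 6 (Group B) sets the end of observation for both arms: 48 hours after the Tritube is placed, "or if the patient deteriorates needing prone-positioning or ECMO therapy". The same section says that blinding is not possible.

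Section 4 names the endpoint without a time point or summary measure: "We choose as the primary endpoint arterial oxygen partial pressure". On timing, section 6 says "In all groups the first clinical data collection starts after 1 hour of initiation", and section 5 says that blood gases "will be collected 6-8 hourly according to clinical standard".

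Section 9 derives 7 patients per group and adds: "However, to compensate for dropouts we will include 10 patients in each group". It does not define a dropout. It names an unpaired t-test or a Mann-Whitney test.

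The secondary outcomes in section 4 run to "Tube obstruction by secretion" and include neither proning nor ECMO. Section 5 does record "clinical data (need for special intervention, e.g. “proning”) drugs used and fluids administered" as well as the timing of ECMO. Section 7 lists the need for proning or ECMO as an exclusion criterion.

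**The concern.** Proning and ECMO follow failing oxygenation, and the primary endpoint measures oxygenation. The rule therefore tends to close a patient's record because the endpoint is poor. If PaO2 is compared late in the 48 hours, the patients still observed are those who did better, and the comparison is no longer between the groups as randomised.

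With no true effect, the arm that loses more patients looks better than it is. If flow-controlled ventilation works and fewer of its patients are stopped, its benefit is understated. Extra enrolment restores numbers but does not change who is missing.

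This cannot be left wholly to an analysis plan, because no analysis can use values that were not collected. Section 8 also deletes the link between identifier and study code at the end of the study. After that, later chart values can no longer be matched to patients.

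**Working it through.** **1. The plan's own figure.** Inputs from section 9: effect 1.5 SD, power 80%, two-sided alpha 5%, 1:1 allocation.

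n per group = 2(1.96 + 0.84)²/1.5² = 6.98, so 7. Then 7/(1 − 0.30) = 10, an implied allowance of 30%. The figure reproduces and is not disputed here. (The normal approximation gives 80% power at 7 per group; the exact t-test gives 73%.)

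**2. Assumptions.** The documents give neither stopping rates nor the link between stopping and PaO2. I assume:
- a share q of an arm is stopped, at most 30%, borrowed from the allowance above;
- stopping has correlation ρ with the compared PaO2 value;
- PaO2 is normally distributed and stopped patients are omitted;
- 10 patients are randomised per arm.

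**3. Shift in an arm's mean when the worst q are lost**, in SD: ρ·φ(z_q)/(1 − q).
- q = 0.30: z = −0.524, φ = 0.348, shift 0.497ρ.
- q = 0.10: z = −1.282, φ = 0.175, shift 0.195ρ.

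**4. No true effect.** Bias favours the arm with more stops. Type I error is from simulation of the t-test.

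| Stopped, one arm vs other | Bias, ρ = 0.5 | Bias, ρ = 1 | Type I error, ρ = 1 |
|---|---|---|---|
| 30% vs 30% | 0 | 0 | about 5% |
| 30% vs 10% | 0.15 SD | 0.497 − 0.195 = 0.30 SD | about 11% |
| 30% vs 0% | 0.25 SD | 0.50 SD | about 16% |

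At ρ = 0.5, type I error for 30% vs 0% is about 7%.

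**5. True effect of 1.5 SD, same threshold in both arms.** The control threshold is −0.524. Relative to the group A mean it is −0.524 − 1.5 = −2.024, so 2.1% of group A stop and the shift there is 0.0525ρ.

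Expected observed difference = 1.5 + ρ(0.0525 − 0.497) = 1.5 − 0.444ρ.

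| ρ | Observed difference | Simulated power |
|---|---|---|
| 0.3 | 1.37 SD | about 73% |
| 0.5 | 1.28 SD | about 70% |
| 1 | 1.06 SD | about 64% |

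This lets treatment shift the stopping tendency by the full 1.5 SD. If treatment affects stopping only through PaO2, the observed difference at ρ = 0.5 is 1.35 SD; at ρ = 1 it is unchanged.

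**6. How much is only loss of numbers.** With 10 per arm analysed, t-test power is 89%. With 10 and 7 analysed and no selection, the noncentrality is 1.5·√(10·7/17) = 3.04 on 15 degrees of freedom, and power is about 81%. So about 8 points of the fall are lost numbers, which the plan already allows for. The rest, from 81% to between 73% and 64%, comes from selection.

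**The case against.** The strongest reply is that the protocol does not prescribe a biased analysis. Four parts of it deserve an answer.

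**Dropouts.** A reader might infer that patients who reach proning or ECMO are the dropouts of section 9 and leave the analysis. The exclusion criterion in section 7 invites that reading, but the text does not support it. Section 9 does not define a dropout, does not refer to the stopping rule and names no analysis set. The word may equally mean withdrawals of consent, which section 8 treats separately. This part stands.

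**Certainty of bias.** A reader might also infer that the difference is bound to be biased. It is not. Sampling starts at 1 hour and repeats, so a patient stopped early usually has PaO2 values. A 1-hour value, a last value or a patient mean would lose few or no patients, and equal stopping with no true effect gives no bias. This stands too, but the protocol commits to none of these and its window runs to 48 hours.

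**An analysis plan not shown.** Handling of the event in the analysis may be set out there, and its absence here is no error. The end of observation, however, is fixed by the protocol itself.

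**Events are recorded.** Proning and ECMO timing are captured, so they can be reported. This is correct. What is missing is their place among the outcomes, and the PaO2 values after them.

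**Conclusion.** The protocol closes observation at an event that is tied to the primary endpoint, open to influence by treatment, and decided by staff who know the arm. A PaO2 comparison late in the 48 hours can therefore be biased, in a direction that depends on which arm loses more patients. Going from 7 to 10 per group does not remove this.

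The size is illustrative, since every stopping rate and correlation is assumed. It ranges from nothing (no true effect, equal stopping) to about 0.5 SD (30% of one arm, none of the other, correlation 1). Figures at correlation 1 are the extreme case and should not be quoted alone.

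In a 20-patient feasibility study this does not invalidate the design. It is an inexpensive correction that changes what the trial can conclude, and it has to be made before data collection closes.

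**What to change.** Leave the clinical rule on proning and ECMO as it is, and amend data collection and analysis:

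1. In section 6, separate the end of study ventilation from the end of data collection. Keep recording the routine 6-8 hourly blood gases and FiO2 to 48 hours after randomisation in all randomised patients. Counting from randomisation also gives group B, which receives no Tritube, a time zero.
2. In section 4, fix the time point or summary of PaO2.
3. In section 9, state that patients who reach proning or ECMO are not dropouts and stay in the comparison in their randomised group.
4. Add proning, ECMO or death by 48 hours as a secondary outcome, compared with the Fisher's exact test already planned.
5. As a sensitivity analysis, give patients with these events the worst ranks and use the Mann-Whitney test already planned.

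**Cost.** Amendment wording and a little more extraction from the electronic chart, done before the identifier link is deleted.

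**Downsides.** PaO2 after the event reflects the added therapy as well as the assigned ventilation. Worst ranks have no mmHg unit, and they let decisions made with knowledge of the arm drive the result, which is why they are not proposed as the primary analysis.

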## **7. Study population and study setting**

All adult patients admitted to the hospital (HMGH, HGH) because of COVID-19 infection who develop a moderate to severe ARDS are eligible.

Inclusion criteria

- Age above 18 years
- Proven COVID-19 infection
- Respiratory failure necessitating intubation and mechanical ventilation
- ARDS with a P/F ratio of at least  $<200\text{mmHg}$  and a PEEP of at least  $>5\text{cmH}_2\text{O}$
- BMI less  $30\text{ kg/m}^2$

Exclusion criteria

- Refuse to sign the consent
- Chronic Respiratory disease
- Acute or chronic Cardiovascular disease
- Pregnancy
- Need for special therapy (prone position and/or ECMO)

We want to ensure there is no risk for our patients. Therefore, we propose a review of our first 4 patients regarding quality and safety by a DMSB. If the IRB agrees we could provide names of intensive care doctors experienced in research.

## **8. Study procedures**

Study duration and timelines

Expected duration of the study: 6 months

Start time: ASAP (April 2020)

Data collection: 1 month

Data-analysis: 3 months

Preparing a publication: 2 months

**Collection of data:**

Demographic data, laboratory data, vital parameters and clinical data will be collected via the electronic patient chart (CERNER).

We will maintain privacy for the subject throughout data collection by carrying out data collection in private rooms. Data confidentiality will be maintained by the use of study IDs rather than any identifying data.

All data will be entered into a secure database, which is password protected with restricted access, only assigned by the research team. Each subject will be assigned an alphanumeric study ID, to ensure data confidentiality. The link between the identifier and the study code will be deleted at the end of the study and the anonymized data set will be kept for at least 5 years after study completion per MRC policy.

#### **Informed consent:**

After explaining the project details, a written informed consent will be obtained from patient/ or family member if the patient is not able to give consent. The family member chosen for the consent will be the one who is patient's next of kin.

